# Comparison of immune cell profiles associated with heatstroke, sepsis, or cardiopulmonary bypass: Study protocol for an exploratory, case-control study trial

**DOI:** 10.3389/fmed.2023.1165786

**Published:** 2023-04-17

**Keywords:** heatstroke, sepsis, cardiopulmonary bypass, immune profile, flow cytometry

## Abstract

**Introduction:**

Heatstroke is a life-threatening illness involving extreme hyperthermia and multi-organ failure, and it is associated with high mortality. The immune profiles of heatstroke have not been fully elucidated, and diagnostic and prognostic biomarkers of heatstroke are lacking. This study will analyze immune profiles in heatstroke patients as they differ from profiles in patients with sepsis or aseptic inflammation patients in order to identify diagnostic and prognostic biomarkers.

**Methods:**

This exploratory, case–control study will recruit patients with heatstroke, patients with sepsis, patients undergoing cardiopulmonary bypass as well as healthy controls at West China Hospital of Sichuan University from 1 January 2023 to 31 October 2023. The four cohorts will be profiled at one time point in terms of lymphocytes, monocytes, natural killer cells, and granulocytes using flow cytometry, and cell populations will be visualized in two dimensions using t-SNE and UMAP, then clustered using PhenoGraph and FlowSOM. Gene expression in the specific immune cell populations will also be compared across the four cohorts, as will levels of plasma cytokines using enzyme-linked immunosorbent assays. Outcomes in the cohorts will be monitored during 30-day follow-up.

**Discussion:**

This trial is, to our knowledge, the first attempt to improve the diagnosis of heatstroke and prediction of prognosis based on immune cell profiles. The study is also likely to generate new insights into immune responses during heatstroke, which may help clarify the disease process and lay the foundation for immunotherapies.

## Introduction

1.

Heatstroke, which can be categorized as classic heatstroke (CHS) or exertional heatstroke (EHS) depending on its cause (1), is the most life-threatening form of hyperthermia (>40.5°C), and it involves central nervous system dysfunction and multi-organ failure (2). Even with intensive care, mortality rates of heatstroke patients can be as high as 30–60% (1, 2). The incidence of heatstroke-related deaths has been increasing globally during the past 2 decades, as record-breaking heatwaves have occurred (1). Heatstroke survivors may experience long-term neurological and cardiovascular complications (1, 2).

Hyperthermia can damage proteins, lipids, and nucleic acids, as well as kill cells directly (3, 4), inducing the production of cytokines to protect against tissue injury (5, 6). If thermoregulation fails to maintain core temperature within an appropriate range, inflammatory responses may become excessive and injure tissue, leading to multi-organ failure and death (7–9), akin to systemic inflammatory response syndrome (SIRS) (10–15). In addition, heatstroke can compromise gastrointestinal integrity, allowing endotoxins and pathogens to enter the circulation and trigger endotoxemia (14). However, potentially informative differences in immune profiles among patients with heatstroke, SIRS, or sepsis have not been fully elucidated.

For lack of a specific biomarker (1), heatstroke is diagnosed based on hyperthermia, history of exposure to extreme heat or vigorous exertion, and alterations of the central nervous system (6, 7). Researchers have undertaken genomic, epigenomic, transcriptomic, proteomic, and metabolomic studies in an effort to identify diagnostic biomarkers (16–18), without much success. The rate of false positive diagnosis of heatstroke remains as high as 24% and the rate of false negative diagnosis as high as 64.5%, especially among patients with atypical symptoms (2). To make matters worse, heatstroke can be difficult to differentiate from sepsis, especially when it involves leukocytosis, which can delay cooling treatments that substantially improve prognosis (1).

Therefore, the aims of this case–control study are to identify the specific immune cells biomarker(s) to diagnose heatstroke and predict prognosis by exploring the immune profile of heatstroke as it differs from profiles in aseptic inflammation and sepsis. The results will help us more comprehensively understand the immune system characteristics of heatstroke, improve its diagnosis, and provide a basis for the development of immunotherapy. In the trial, patients with heatstroke, patients with sepsis, patients undergoing cardiopulmonary bypass [CPB, representative of aseptic inflammation (19)], and healthy controls will be compared in terms of their profiles of lymphocytes, monocytes, natural killer cells, and granulocytes in circulation, based on flow cytometry; in terms of gene expression in different immune cell populations, based on single-cell RNA sequencing; and in terms of cytokine levels in plasma, based on enzyme-linked immunosorbent assay (ELISA). The three cohorts of patients will be matched according to age, sex, weight, and comorbidities. Healthy controls will be matched to heatstroke patients based on age, sex and weight.

## Methods and analysis

2.

The protocol of this exploratory, case–control study has been approved by the Medical Ethics Committee of West China Hospital, Sichuan University (2022–1408), and it has been registered at the Chinese Clinical Trial Registry^1^ under ChiCTR-2200066952. This protocol follows the SPIRIT guidelines, and the SPIRIT checklist was provided in Supplementary Table 1. The study will be coordinated by the International Medical Center and by the Departments of Anesthesiology and of Emergency Medicine at West China Hospital of Sichuan University (Figure 1).

**Figure 1 fig1:**
[figure not shown]
Presentation of the study design.

### Participant selection and matching

2.1.

#### Inclusion and exclusion criteria

2.1.1.

Participants will be recruited from the International Medical Center and from the Departments of Emergency Medicine and of Anesthesiology at West China Hospital of Sichuan University. Four cohorts of 40 individuals each will be recruited: heatstroke patients, sepsis patients, patients undergoing CPB, and healthy controls. The inclusion and exclusion criteria for each cohort are shown in Table 1. Participant recruitment and data collection will begin on January 1, 2023 and will continue until October 31, 2023.

**Table 1 tab1:** Inclusion and exclusion criteria for subject enrollment.

Subjects	Inclusion criteria	Exclusion criteria
Heatstroke patients	(1) Age ≥ 18 years	(1) Pregnant women.
	(2) History of exposure to extreme environmental heat or vigorous muscle exertion	
	(3) Core body temperature > 40°C or symptoms of central nervous system (CNS) dysfunction, such as coma, delirium, or convulsions	(2) Comorbid with immune system disease within the 6 months prior to admission, including but not limited to acquired immune deficiency syndrome (AIDS), multiple myeloma, rheumatoid arthritis, systemic lupus erythematosus, multiple sclerosis, myasthenia gravis, scleroderma, Crohn’s disease, and ulcerative colitis.
	(4) Written informed consent to participate	
Sepsis patients	(1) Age ≥ 18 years	(3) Comorbid with malignant tumor and hematological diseases.
	(2) Suspected or known infection	
	(3) Sequential organ failure assessment (SOFA) score ≥ 2	
	(4) Written informed consent to participate	(4) History of organ or bone marrow transplantation.
Patients undergoing CPB	(1) Age ≥ 18 years	
	(2) Valve replacement or coronary artery bypass under cardiopulmonary bypass	
	(3) Written informed consent to participate	
Healthy controls	(1) Age ≥ 18 years	(5) History of immunosuppressive therapy, including glucocorticoids, soluble microbial products (SMSs), polyclonal and monoclonal antibodies, antimetabolite and alkylating agents, or radiotherapy within the 6 months prior to admission.
	(2) Body mass index 18–24 kg/m^2^	
	(3) Health examination within the previous 6 months indicated no abnormality	
	(4) Written informed consent to participate	

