#### Participant matching

2.1.2.

Heatstroke patients will be matched 1:1 with sepsis patients, CPB patients and healthy controls using propensity score analysis based on nearest-neighbor matching and a caliper width of 0.2 of the standard deviation of the logit of the propensity score (20). Covariates during matching of heatstroke and sepsis patients will be sex, age, body weight, Sequential Organ Failure Assessment (SOFA) score (21), comorbidities, and treatment history. Covariates during matching of heatstroke and CPB patients will be sex, age, body weight, comorbidities, and treatment history. Covariates during matching of heatstroke patients and healthy controls will be sex, age, and body weight.

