## Discussion

3.

This trial aims to be the first systematic, comprehensive comparison of immune cell profiles across three conditions that can be difficult to differentiate clinically: heatstroke, aseptic inflammation such as in patients undergoing CPB (19), and systemic infection such as in sepsis patients. Our study may succeed in identifying specific immune cell signatures useful for accurate diagnosis of heatstroke and for identifying patients at high risk of worse outcomes. Regardless of whether the study achieves this goal, it should provide a comprehensive understanding of the immune profiles in heatstroke, which may help clarify the course of this life-threatening condition and lay the foundations for immunotherapies that might become the first curative treatments for heatstroke.

To reduce the potential bias of clinicodemographic differences among the four cohorts on their immune cell profiles, we will match the groups based on age, sex, and body mass index.

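### The sepsis cohort is matched on total SOFA but not on temperature or CNS status, so the planned ROC accuracy may not apply to the patients who are hard to tell apart

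*Protocol article*

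**What the plan says.** The Introduction of the protocol article gives the clinical problem: "heatstroke can be difficult to differentiate from sepsis, especially when it involves leukocytosis", with delayed cooling as the consequence. The Discussion describes the comparison as running "across three conditions that can be difficult to differentiate clinically".

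Table 1 (section 2.1.1) sets entry as follows.
- Heatstroke: "History of exposure to extreme environmental heat or vigorous muscle exertion", together with "Core body temperature > 40°C or symptoms of central nervous system (CNS) dysfunction, such as coma, delirium, or convulsions". Either the temperature or the CNS sign is enough.
- Sepsis: "Suspected or known infection", together with "Sequential organ failure assessment (SOFA) score ≥ 2". There is no temperature or CNS criterion.

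On matching, section 2.1.2 states: "Covariates during matching of heatstroke and sepsis patients will be sex, age, body weight, Sequential Organ Failure Assessment (SOFA) score", followed by comorbidities and treatment history. Matching is 1:1, nearest neighbour, within a caliper. Neither admission temperature nor CNS status is listed.

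Section 2.5 plans ROC curves for immune cell subsets with Youden thresholds, and sensitivity, specificity, predictive values and likelihood ratios. Table 2 schedules symptoms and vital signs on admission for both the heatstroke and the sepsis cohort.

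**The concern.** Accuracy depends on the mix of patients in whom it is measured. Heatstroke cases are selected on a presentation that sepsis patients need not have. A cell subset that responds to high temperature or to CNS involvement, whatever the cause, could then separate the cohorts without carrying information about heatstroke itself. Such a subset would rank well on the ROC curve and fail in a feverish or confused patient for whom the clinician must choose between the two diagnoses. That is the decision the study says it wants to improve.

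**Working it through.** The plan has no figure to reproduce. The cohort size of 40 is stated without a power calculation, and no target AUC, sensitivity or specificity is given. The main check is a reading of the criteria; the arithmetic only shows what size is possible.

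**1. Criteria side by side.** Every heatstroke case has at least one of temperature above 40°C or a CNS sign. A sepsis patient may have both, one or neither. Matching on total SOFA aligns overall organ-failure severity, but the same total can come from different organs, so CNS status is not aligned. Temperature is not in the matching model.

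**2. Model based on the share of sepsis patients with the presentation.** Assumed inputs, none from the documents:
- q, the share of sepsis patients with the presentation: 20%, 50% or 80%
- b, the response of the marker to the presentation: 0.5, 1.0 or 1.5 SD
- s, its response to heatstroke itself: 0 or 0.5 SD

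All heatstroke cases are taken to have the presentation, treated as a single trait. Then

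AUC against all sepsis = q·Φ(s/√2) + (1−q)·Φ((b+s)/√2), and AUC against sepsis with the same presentation = Φ(s/√2).

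| s | b | q = 20% | q = 50% | q = 80% | same presentation |
|---|---|---|---|---|---|
| 0 | 0.5 | 0.611 | 0.569 | 0.528 | 0.500 |
| 0 | 1.0 | 0.708 | 0.630 | 0.552 | 0.500 |
| 0 | 1.5 | 0.784 | 0.678 | 0.571 | 0.500 |
| 0.5 | 0.5 | 0.736 | 0.699 | 0.663 | 0.638 |
| 0.5 | 1.0 | 0.812 | 0.747 | 0.682 | 0.638 |
| 0.5 | 1.5 | 0.865 | 0.780 | 0.695 | 0.638 |

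Inflation runs from 0.663 − 0.638 ≈ 0.02 to 0.784 − 0.500 ≈ 0.28. It goes to zero as q approaches 1 or b approaches 0.

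**3. Model based on temperature alone.** Assume mean admission temperatures of 40.5 and 38.2°C, SD 0.9 in each cohort, and a marker with no heatstroke-specific signal that correlates r with temperature within cohort. Then d = r × (40.5 − 38.2)/0.9 = 2.556r. For r = 0.2, 0.3 and 0.5, d = 0.51, 0.77 and 1.28, and AUC = Φ(d/√2) = 0.64, 0.71 and 0.82. At equal temperature the AUC is 0.50 by construction.

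**4. A bias in the other direction.** The entry criteria are not mutually exclusive: a delirious, infected patient with heat exposure can meet both sets. If a share c of the heatstroke cohort were really septic, a true AUC of 0.80 would become (1−c)·0.80 + c·0.50. That is 0.77 at c = 10% and 0.71 at c = 30%.

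**5. Precision of a restricted analysis.** With 40 heatstroke cases and q = 20%, 50% or 80%, 8, 20 or 32 sepsis patients remain. The Hanley–McNeil standard error at AUC 0.5 is 0.113, 0.080 or 0.069, so the 95% half-width (1.96 × SE) is about 0.22, 0.16 or 0.14. With all 40 it is 1.96 × 0.065 ≈ 0.13.

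**The case against.** The strongest reply is the SOFA matching. An alert sepsis patient with a normal temperature does not become a comparator automatically; that patient must fall within the caliper of a heatstroke case on a score that includes severity. This stands, and it removes part of any easy contrast. It does not align CNS status or temperature.

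Second, the Introduction ties the confusion to leukocytosis and misdiagnosis to atypical symptoms, so treating shared fever or CNS dysfunction as the mark of the doubtful patient is partly an inference. That is fair. But leukocytosis is not a sepsis entry criterion or a matching covariate either, so on that reading too the cohort is not built to be the doubtful group.

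Third, a reader might point to heat shock protein-72 as an obvious temperature marker. It is a plasma ELISA analyte (section 2.4.4), whereas the ROC plan concerns immune cell subsets. The documents do not show that any given subset tracks temperature or coma; the concern is conditional on that. Blood may also be drawn at any time within 24 h after admission, which loosens the link with admission temperature.

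Fourth, the study is exploratory, and a broad sepsis comparator is defensible for discovery. A subset analysis may also sit in a full protocol or analysis plan that is not shown, and its absence from the article is not the point made here. The point rests on the stated eligibility and matching choices, set against the stated purpose and the accuracy measures planned.

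**Conclusion.** The point holds as a limit on what the accuracy results can mean. The sepsis cohort is neither required nor matched to share the presentation by which heatstroke cases are selected. ROC results may therefore be inflated for subsets that track that presentation, and may not transfer to patients in whom the diagnosis is in doubt.

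The size cannot be fixed, because the protocol gives no temperature or CNS distribution for either cohort. The 0.02 to 0.28 range, and the 0.64 to 0.82 from the temperature model, rest wholly on assumed inputs.

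A reader might infer that accuracy will certainly be overstated, or that the study cannot show usefulness where diagnosis is uncertain. The documents support neither. Sepsis patients may well have fever or CNS signs, SOFA is matched, overlapping criteria could lower apparent accuracy, and the admission data needed for a sharper analysis are collected. Nor are heatstroke cases selected on fever and CNS dysfunction together: either one suffices, and heat exposure or exertion is also required.

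**What to change.** Keep the full SOFA-matched sepsis contrast. Prespecify, if the full plan does not already do so, a heatstroke v sepsis accuracy analysis stratified by, or limited to, sepsis patients with high fever or CNS dysfunction on admission. Use the vital signs and symptoms in Table 2 and give confidence intervals. The article sets no threshold for high fever in sepsis, so the stratum must be defined before marker data are seen. Where feasible, direct sepsis recruitment toward such patients so that the stratum is not too small.

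Base any claim of diagnostic use on that stratum, and present the unselected sepsis, CPB and healthy contrasts as exploratory immune profiling. If discrimination is reported alongside admission temperature, add the caveat that temperature is part of the heatstroke case definition, so its own apparent accuracy is partly built in.

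The data cost is nil for the analysis and modest for directed recruitment, which may slow sepsis enrolment. The statistical cost is a smaller and less precise stratum, partial loss of the 1:1 matching within it, and probably a less favourable AUC.

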### Endpoints

2.2.

The aims of this case–control study are to identify the diagnostic immune cells biomarker(s) of heatstroke and prognostic immune cells biomarker(s) of heatstroke within 30 days.

For exploring diagnostic biomarker(s) that distinguishes patients with heatstroke from patients with sepsis, patients with aseptic inflammation and healthy individuals, because this trial is a case–control study, no endpoints can be provided.

For exploring prognostic biomarker(s) for patients with heatstroke, the primary endpoint is all-cause mortality within 30 days. The secondary endpoints include incidence of the organ injury events within 30 days, including neurological dysfunction, acute heart failure, acute renal failure, or respiratory failure, which are diagnosed as following:

Neurological dysfunction will include stroke, which will be diagnosed based on symptoms of unconsciousness or focal neurologic deficit and the results of computerized tomography and magnetic resonance imaging; and delirium, which will be diagnosed as described (22).

Acute heart failure will be diagnosed according to symptoms of breathlessness, tiredness, and fatigue; clinical signs; abnormalities of electrocardiogram(ECG) such as atrial fibrillation, Q waves, left ventricle hypertrophy, and a widened QRS complex (23); left ventricular ejection fraction (LVEF) ≤ 40% based on the results of echocardiography (23); and elevated levels of B-type natriuretic peptide (BNP) or NT-proBNP (24).

Acute renal failure will be defined as stage 3 acute kidney injury according to the KDIGO criteria (25): stage3: creatinine level in serum ≥4.0 mg/dL (353.60 μmol/L) or ≥ 3 times baseline within 7 days, or requirement for renal replacement therapy, or urine output <0.3 mL/kg/h for ≥24 h OR anuria for ≥12 h.

Respiratory failure will be defined as pH < 7.35 and PaCO_2_ > 45 mmHg or as PaO_2_/FiO_2_ < 200 based on invasive or non-invasive ventilation or arterial blood gas analysis (26, 27) within 30 days. If patients with concomitant pulmonary diseases prior to admission meet above diagnostic criteria, the patient will not be considered to have lung injury caused by heatstroke and will be excluded.

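### The CPB cohort is the aseptic-inflammation comparator, but Table 1 does not exclude infected patients from it or separate it from the sepsis cohort

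*Protocol article*

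**What the plan says.** **Role of the cohort.** The Introduction describes the group as "patients undergoing cardiopulmonary bypass [CPB, representative of aseptic inflammation (19". The Discussion repeats the contrast: "aseptic inflammation such as in patients undergoing CPB (19), and systemic infection such as in sepsis patients". Section 2.2 (Endpoints) builds the diagnostic aim on it, seeking a biomarker that "distinguishes patients with heatstroke from patients with sepsis, patients with aseptic inflammation and healthy individuals".

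**Who may enter.** Section 2.1.1 presents Table 1 as the inclusion and exclusion criteria for each cohort. Besides adult age and consent, a CPB patient needs only "2) Valve replacement or coronary artery bypass under cardiopulmonary bypass". The indication for surgery is not restricted. The exclusions cover pregnancy, immune system disease in the prior 6 months, malignant or haematological disease, transplantation, and immunosuppressive therapy in the prior 6 months.

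**Who counts as septic.** Table 1 defines the sepsis cohort by infection, suspected or confirmed, together with SOFA ≥ 2.

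**The concern.** Absence of infection is the property that gives the CPB cohort its purpose. Sepsis represents infectious inflammation and CPB represents sterile inflammation, and a heatstroke signature is to be read against both. The criteria do not secure that property. A patient having an infected valve replaced, or one who comes to surgery with another active infection, is eligible as written. Endocarditis is an example supplied here; the document does not mention it, but nothing in Table 1 bars it.

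What is at stake is the meaning of the heatstroke-versus-CPB comparison. If some CPB patients are infected, a difference or similarity between heatstroke and CPB reflects a blend of two kinds of inflammation. The Introduction itself says that heatstroke can let endotoxins and pathogens into the circulation and can be hard to tell from sepsis. Markers on which heatstroke resembles infection are therefore plausible, and those are the markers for which the blend matters.

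**Working it through.** **Step 1. Does any criterion remove infected CPB patients?**

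- Exclusions in Table 1: none of the five names active infection, sepsis or an infectious surgical indication. AIDS, listed under immune disease, is the only infection-related item.
- Mutual exclusivity: no rule states that a patient meeting the sepsis criteria cannot be enrolled as a CPB patient. A valve patient with infection and SOFA ≥ 2 satisfies both definitions.

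**Step 2. Does anything later remove them?**

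- Matching (section 2.1.2): the heatstroke–CPB covariates are demographics, weight, comorbidities and prior treatment. SOFA is used only for heatstroke–sepsis. The comorbidity list in section 2.4 names viral infection and no bacterial infection.
- Data collection (section 2.4): surgical diagnosis is recorded for CPB patients, but no rule uses it for eligibility. Infection is otherwise a 30-day follow-up item.
- Sampling (section 2.4.1): CPB blood is drawn at the end of bypass, so an infection present at surgery is already in the sample.

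No step in the document closes the gap.

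**Step 3. How many patients?** The document gives no infected share p, so the values below are assumptions. With n = 40 (section 2.1.1), the expected number is 40p and the chance of at least one is 1 − (1 − p)^40.

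| assumed p | expected infected | chance of at least one |
|---|---|---|
| 2% | 0.8 | 55% |
| 5% | 2 | 87% |
| 10% | 4 | 98.5% |
| 20% | 8 | >99.9% |

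**Step 4. Effect on the planned ROC analysis.** Section 2.5 assesses how well cell subsets predict heatstroke, so the relevant contrast is heatstroke versus CPB. With a share p of infected CPB patients:

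AUC observed = (1 − p) × AUC(heatstroke v sterile CPB) + p × AUC(heatstroke v infected CPB)

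Take a true AUC of 0.90 against sterile CPB.

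- Marker equally good against infected CPB (0.90): (1 − p) × 0.90 + p × 0.90 = 0.90 for every p. No bias.
- Marker somewhat weaker against infected CPB (0.80), p = 10%: 0.90 × 0.90 + 0.10 × 0.80 = 0.89.
- Marker that does not separate heatstroke from infection (0.5):
  - p = 5%: 0.95 × 0.90 + 0.05 × 0.5 = 0.88
  - p = 10%: 0.90 × 0.90 + 0.10 × 0.5 = 0.86
  - p = 20%: 0.80 × 0.90 + 0.20 × 0.5 = 0.82

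The value 0.5 is an assumption about how infected CPB patients look, not a figure from the document.

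**Step 5. Scale against sampling error.** With 40 per group, the Hanley–McNeil standard error at AUC 0.90 is about 0.036. The losses of 0.02, 0.04 and 0.08 are about 0.6, 1.1 and 2.2 standard errors.

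**The case against.** The case on the other side has four parts.

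- **The effect may be small.** At 5% infected, even the unfavourable marker moves by less than one standard error, and a marker that separates heatstroke from both kinds of inflammation is untouched. A marker that fails against infection should also fail in the sepsis comparison, where this would be seen. This stands, and it limits the point to interpretation of the sterile contrast. It does not remove the point, because the bias is systematic and larger enrolment would not reduce it.
- **Infection is not sepsis.** A reader might infer that the CPB cohort will contain septic patients. The document supports only that it can: SOFA ≥ 2 is also needed, and the case mix is not given.
- **The data allow repair.** Surgical diagnosis, antibiotic use and laboratory results are recorded. This is true and makes the problem recoverable, but no stated rule uses them to keep the cohort aseptic.
- **This is a condensed article.** Screening details may sit in a fuller protocol. However, Table 1 is presented as the criteria themselves and goes as far as naming individual autoimmune diseases. The objection is to a comparator whose stated definition does not match its label.

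Two further readings are tempting and not supported. A reader might infer that a few infected patients would form their own cluster in the cytometry data, but section 2.4.3 clusters cells, not patients. A reader might also extend the point to healthy controls, because "3) Health examination within the previous 6 months indicated no abnormality" can predate the blood draw. That requires reading the healthy-control label as admitting someone acutely ill on the day, which is strained, and nothing in the document gives it a size.

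**Conclusion.** The point holds as a defect in the CPB eligibility criteria. As written, Table 1 lets infected patients, some of whom could also meet the sepsis criteria, into the cohort meant to represent sterile inflammation, and nothing later in the document removes them.

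The size cannot be fixed from the document. It ranges from no bias to a fall in heatstroke-versus-CPB AUC from 0.90 to 0.82. The lower end needs both an assumed 20% infected share and a marker with no ability to separate heatstroke from infection.

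A reader might infer that the study could no longer tell sterile from infectious inflammation at all. That goes too far: at small infected shares the shift is within sampling error, and the separate sepsis cohort still informs the question. The correction is worth making because it is specific, cheap and protects a central comparator.

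**What to change.** In Table 1, add an exclusion for the CPB cohort: known or suspected active infection at the time of surgery, including an infectious indication for the operation, or meeting the sepsis cohort criteria. Because the sepsis definition requires infection, the first part already covers the overlap; the second makes the two cohorts explicitly exclusive.

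For CPB patients already enrolled, use the recorded surgical diagnosis and laboratory results to identify any who would have been excluded. Leave them out of the aseptic comparison and repeat the 1:1 matching in section 2.1.2. Antibiotic use is a weaker screen than surgical diagnosis and should only support it.

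The cost is one line in Table 1, a few otherwise eligible valve patients, and some re-matched pairs. If removals take the cohort below 40, replacements would have to be recruited within the window ending 31 October 2023, or the shortfall reported.
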